| Background                | COVID-19 caused by SARS-CoV-2 is an unprecedented global public health challenge which as at 24 May 2020 has spread to over 210 countries with over 5.31 million cases including 342,000 deaths. More than 1130 clinical trials are currently ongoing in an unprecedented global search for potential therapeutics and vaccines. |
| Objectives                | The purpose of this phase 2 trial is to investigate the efficacy and safety of repurposed antiprotozoal and antiretroviral drugs, nitazoxanide and atazanavir/ritonavir, in achievement of SARS-CoV-2 PCR negativity and shorten the time to clinical improvement in patients diagnosed with moderate to severe COVID-19.        |
| Recruitment               | Individuals between 18 and 75 years old who receive a PCR positive test for COVID-19 and admitted at participating COVID-19 treatment centres will be invited to participate.                                                                                                                                                    |
| Sample Size               | 98                                                                                                                                                                                                                                                                                                                               |
| Randomisation             | For this pilot study, consenting individuals will be randomised 1:1 to receive either standard of care (SOC) alone (n = 49) or SOC plus daily trial intervention (n = 49).                                                                                                                                                       |
| Intervention              | Arm 1: SOC
Arm 2: SOC + 1000 mg nitazoxanide twice daily and 300/100 mg atazanavir/ritonavir once daily with meal for 14 days                                                                                                                                                                                                 |

ObjectivesOutcome Measures

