3. Established safety record: Nitazoxanide is an antiprotozoal drug with a well understood and documented safety profile. It was first approved by the US Food and Drug Administration (FDA) in July 2004 for the treatment of diarrhea caused by *Giardia lamblia* or *Cryptosporidium parvum* in adults ( $\geq 18$  years) and paediatrics (1-17 years). Safety information from 1628 adults and adolescents who received nitazoxanide tablets in controlled and uncontrolled studies reported no death and adverse events included abdominal pain (6.7%), diarrhoea (4.3%), headache (3.1%), nausea (3.1%) and dizziness (1%). No grade 4 or 5 adverse events were reported. Single oral doses of up to 4000 mg nitazoxanide have been administered to healthy adult volunteers without significant adverse effects. A 1000 mg twice daily dosage for 14 days has been reported and found to be safe. No safety issues were identified at doses up to 3000 mg/day for a median of 62 days (range: 1-1528) in AIDS-related cryptosporidiosis. Though no evidence of teratogenicity was observed in animals treated with multiple times the clinical adult dose adjusted for body surface area, nitazoxanide safety during human pregnancy or lactation has not been evaluated. Also, it has not been studied in patients with renal or hepatic impairment.

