## **4. Safety Assessment**

Participants will be assessed for adverse events daily throughout study period. Each morning the attending physician will ask about the side effects commonly associated of nitazoxanide (including gastrointestinal symptoms and headaches) and any additional symptoms using a structured questionnaire. Staff at the treatment centre will further assess participants for the occurrence of new symptoms at least every six hours. Adverse events will be graded according to the NIH Division of AIDS grading scale (Appendix 6) and causality will be determined using Liverpool Causality Assessment Tool (Appendix 7). All serious adverse events, including those resulting in discontinuation of trial intervention, whether or not they are judged to be related to the trial, will be recorded as per trial schedule of follow up activities. All safety issues will be reviewed after the first 15 participants in the intervention group have completed 14 days of follow up and when any grade 3 or higher adverse event occurred in the intervention group.

**Table 1.** Schedule of Follow Up Activities

| Procedure                                             | Day 0 | Day 1 | Day 2 | Day 3 | Days 4-6 | Day 7 | Days 8-9 | Day 10 | Days 11-13 | Day 14 | Day 21 | Day 28 |
|-------------------------------------------------------|-------|-------|-------|-------|----------|-------|----------|--------|------------|--------|--------|--------|
| Informed consent                                      | X     |       |       |       |          |       |          |        |            |        |        |        |
| Demography                                            | X     |       |       |       |          |       |          |        |            |        |        |        |
| Medical history (recent and current)                  | X     |       |       |       |          |       |          |        |            |        |        |        |
| Pregnancy test (for reproductive age women)           | X     |       |       |       |          |       |          |        |            |        |        |        |
| Concomitant medications                               | X     |       |       |       |          |       |          |        |            |        |        |        |
| Physical examination                                  | X     |       |       |       |          |       |          |        |            |        |        |        |

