Abbreviations: ECMO, Extracorporeal membrane oxygenation; NIV, Non-invasive ventilation;  $\text{FiO}_2$ , Fraction of inspired oxygen;  $\text{PaO}_2$ , pressure of arterial oxygen;  $\text{SpO}_2$ , oxygen saturation

- Time to PCR negativity. Proportion of participants with SARS-CoV-2 polymerase chain reaction (PCR) negative result at Days 7, 10, 14 and 28.
- Temporal patterns of SARS-CoV-2 viral load quantified by RT-PCR from nasal swabs or sputum of patients receiving SOC alone versus SOC plus study drug.

Secondary outcome measures:

- Time to symptoms resolution as monitored by the inFLUenza Patient-Reported Outcome (FLU-PRO) questionnaire with some modifications for COVID-19 (Appendix 8).
- Clinical status as assessed with the 10-category ordinal scale on days 7 and 14
- Duration of hospitalization in survivors
- Day 28 mortality
- Time from treatment initiation to death
- Proportion with viral RNA detection over time

 Note:  $\text{PaO}_2/\text{FiO}_2$  of 200-300, mild ARD; 100-200, moderate ARD; <100, severe ARD

Safety outcome measures:

- Adverse events during treatment
- Serious adverse events (respiratory failure or Acute Respiratory Distress Syndrome (ARDS), acute kidney Injury (AKI), secondary infection, shock, severe anemia, acute gastritis, unconsciousness, sepsis, acute heart failure)
- Gastrointestinal adverse events (nausea, vomiting, and diarrhea)
- Premature discontinuation of treatment

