All subjects experiencing AEs, whether considered associated with the use of the study medication or not, must be monitored until the symptoms subside and any clinically relevant changes in laboratory values have returned to baseline, or until there is a satisfactory explanation for the changes observed. Procedures such as surgery should not be reported as AEs. However, the medical condition for which the procedure was performed should be reported if it meets the definition of an AE. For example, an acute appendicitis that begins during the AE reporting period should be reported as the adverse event and the resulting appendectomy noted on the CRF. Planned procedures such as surgery planned prior to the subject's enrolment into the study need not be reported as AEs if these are documented as planned at the screening visit. *Clinically significant* changes in physical examination and blood safety profiles should also be recorded as AEs. Severity should be recorded and graded according to the Division of AIDS Table for Grading the Severity of Adult and Paediatric Adverse Events.

All AEs, however minor, will be documented in the CRF whether or not the Investigator concludes the event to be related to drug treatment. The AE reporting period will be from the screening visit until the subject's final study visit. In addition, any untoward event that may occur subsequent to the reporting period that the Investigator assesses as possibly, probably or definitely related to the study drug medication should also be reported as an AE. AEs may be directly observed, reported spontaneously by the subject or by questioning the subject at each study visit. All AEs should be followed up until they are resolved or the subject's participation in the study ends (i.e. until the final CRF is completed for that subject). In addition, all serious and non-serious AEs assessed by the Investigator as possibly related to the investigational medication should continue to be followed even after the subject's participation in the study is over. Such events should be followed until resolution, or until no further change can reasonably be expected. Deaths occurring

---

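### The gastrointestinal safety outcome names nausea, vomiting and diarrhoea but not abdominal pain, the most frequent nitazoxanide adverse event the protocol cites

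*Protocol*

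**What the plan says.** The protocol touches on gastrointestinal tolerability in four places.

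- **Section 5 (Outcome Measures, safety outcomes)** has four entries. One is "Gastrointestinal adverse events (nausea, vomiting, and diarrhea", where the three terms in the bracket complete the entry. Another is the general outcome, "Adverse events during treatment".
- **Section 2.1 (Nitazoxanide, established safety record)** summarises experience in 1628 adults and adolescents from controlled and uncontrolled studies: "adverse events included abdominal pain (6.7%), diarrhoea (4.3%), headache (3.1%), nausea (3.1%) and dizziness (1" percent. Vomiting is given no rate.
- **Section 4 (Safety Assessment)** has the physician ask each morning about "the side effects commonly associated of nitazoxanide (including gastrointestinal symptoms and headaches", plus any additional symptoms, with a structured questionnaire. Events are graded on the DAIDS scale.
- **Section 21 (Adverse Events Management)** requires that every adverse event, however minor, "will be documented in the CRF whether or not the Investigator concludes the event to be related to drug treatment".

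**The concern.** The list in Section 5 does not follow the safety evidence in Section 2.1. It leaves out the gastrointestinal event with the highest cited rate and includes one, vomiting, for which no rate is cited. Section 4 asks about gastrointestinal symptoms without restricting them to three terms, so what is asked is broader than what this outcome counts.

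Of the four safety outcomes, this is the only one devoted to gastrointestinal tolerability; acute gastritis appears only inside the serious adverse event entry. If the three terms are applied as written, a participant with abdominal pain alone, of any grade, has no gastrointestinal adverse event for this outcome. A results row under that title would look complete to a reader when it is not.

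This is also not merely a detail left for an analysis plan, because the protocol itself names the component terms. A plan that follows the protocol would carry the omission forward. A plan that adds abdominal pain would depart from the protocol's stated outcome.

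**Working it through.** **Inputs**

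| Quantity | Value | Source |
|---|---|---|
| Abdominal pain | 6.7% | Section 2.1 |
| Diarrhoea | 4.3% | Section 2.1 |
| Nausea | 3.1% | Section 2.1 |
| Vomiting | no rate given | – |
| Intervention arm | 49 | Trial Synopsis |

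The 6.7% is cited without a numerator, so it cannot be reproduced; I take it as given. Section 2.1 lists five rates (headache at 3.1% and dizziness at 1% are the other two), and abdominal pain ranks first among them.

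**Step 1. Expected patients with each term** = rate × 49.

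- Abdominal pain: 0.067 × 49 = 3.28
- Diarrhoea: 0.043 × 49 = 2.11
- Nausea: 0.031 × 49 = 1.52

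The chance of at least one patient with abdominal pain is 1 − (1 − 0.067)^49 = 0.97, so the question of how to count it would very probably arise.

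**Step 2. Patients the outcome would miss.** A patient is missed only if abdominal pain occurs without any listed term. The documents do not say how the terms overlap, so only bounds can be given.

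- *Upper bound, no overlap:* every patient with abdominal pain is missed, 3.28 of 49. The outcome rate from diarrhoea and nausea is 4.3% + 3.1% = 7.4% (3.63 patients). With abdominal pain it is 7.4% + 6.7% = 14.1% (6.91 patients).
- *Lower bound, every patient with pain also has a listed term:* 0 missed. This is arithmetically possible, because diarrhoea and nausea can together affect up to 7.4% of patients, which exceeds 6.7%.
- *Between the bounds, for illustration:* if the terms occurred independently, the rate is 1 − 0.957 × 0.969 = 7.27% for diarrhoea or nausea, and 1 − 0.957 × 0.969 × 0.933 = 13.48% with abdominal pain. The difference is 6.21%, or 0.0621 × 49 = 3.04 patients.

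Leaving vomiting out makes these figures generous to the concern, since some patients with abdominal pain could be counted through vomiting.

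**Step 3. Share of reports.** 6.7 / (6.7 + 4.3 + 3.1) = 6.7 / 14.1 = 47.5%. This is a share of summed term frequencies, not of patients, and it leaves out vomiting.

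**Step 4. Difference between arms.** Section 2.1 gives no rate in a comparator group, and the protocol gives no rate of abdominal pain under standard of care. Neither the size nor the direction of any change in the between-arm difference can be calculated.

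**The case against.** The strongest objection is that the bracket may be illustrative. The neighbouring entry in Section 5 has the same form: serious adverse events followed by a bracketed list of conditions. That list cannot be exhaustive, because Section 21.1 defines seriousness by six general criteria, including death, which the list does not contain. On that pattern, nausea, vomiting and diarrhoea could be examples too. This stands as a reason not to be certain of the literal reading. It does not settle the matter: nothing in the gastrointestinal line marks it as open, whereas Section 4 does write "including gastrointestinal symptoms and headaches) and any additional symptoms using a structured questionnaire" when it means an open list.

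The second objection is that abdominal pain is already covered. This is correct as far as safety reporting overall is concerned. It is asked about, recorded, graded and reported under the general outcome. Only the dedicated gastrointestinal outcome is affected.

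Three stronger readings are tempting, and the documents do not support them.

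- *A reader might infer that the omission shrinks the difference between arms.* That would require abdominal pain without a listed term to be commoner on study drug than on standard of care. The rates in Section 2.1 come partly from uncontrolled studies and have no comparator.
- *A reader might infer that the outcome loses nearly half of the gastrointestinal events, about 3.3 of 6.9.* That counts reports rather than patients, assumes no overlap, and ignores vomiting. The loss in patients is anywhere from 0 to about 3.3.
- *A reader might infer that abdominal pain must be added to the daily questionnaire.* The questionnaire is not shown, so it may already be there.

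Finally, the cited rates are for nitazoxanide tablets. The protocol gives no adverse event rates for atazanavir/ritonavir or for the combination, so abdominal pain is the most frequent cited event for nitazoxanide, not a demonstrated leading event for this regimen.

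**Conclusion.** The point holds in a limited form. As worded, the gastrointestinal outcome does not include the most frequent nitazoxanide adverse event that the protocol itself cites, and a literal count would leave out participants who have abdominal pain alone. The undercount in the intervention arm is 0 to about 3.3 of 49 patients. This assumes that the Section 2.1 rates carry over to this population and combination, that the full arm of 49 is treated, and that vomiting is set aside for want of a rate. The effect on the comparison between arms is unknown. No sample size, power or primary outcome is affected, and abdominal pain remains visible in the general adverse event reporting. It is worth correcting because the wording allows two counts of the same outcome and the correction is nearly free.

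**What to change.** In Section 5, redefine the entry as any gastrointestinal adverse event, including abdominal pain, nausea, vomiting and diarrhoea, reported by arm and by maximum DAIDS grade. If the three terms were meant only as examples, the same wording makes that clear.

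The cost is one line of protocol text. Sections 4 and 21 already provide for collecting and grading these events, so no visit, sample or data item is added. The only downside is that the reported gastrointestinal event rate will be somewhat higher than under the three-term count.

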## 6. Power and Sample Size Determination

As shown in Figure 3, the sample size estimation is based on the assumption that an improvement of at least 60-80% in time to SARS-CoV-2 PCR negativity and symptoms resolution can be achieved in the intervention group compared with the control group. Hence, a total sample size of 89 will provide at least 80% power to show or exclude 60% improvement in time to SARS-CoV-2 PCR negativity. This assumes a two-sided and 5% type 1 error rate. Therefore, providing for a 10% loss to follow up rate, a total of 98 patients will be recruited.

[figure not shown]

**Figure 3.** Power calculation and sample size estimation.

## 7. Study Sites and Population

Individuals (female or male) with confirmed COVID-19 test confirmed by PCR will be identified from the following isolation and treatment centres in Nigeria:

- Infectious Diseases Hospital, Olodo, Ibadan, Oyo State

- Obafemi Awolowo University Teaching Hospital, Ile-Ife, Osun State
- Specialist State Hospital, Asubiaro, Osogbo, Osun State
- Olabisi Onabanjo University Teaching Hospital, Sagamu, Ogun State

Eligibility will be ascertained using the following inclusion and exclusion criteria:

#### **7.1. Inclusion criteria**

- Willingness and ability to provide written informed consent.
- At least 18 and not more than 75 years of age at study entry.
- SARS-CoV-2 infection confirmed by PCR test within 2 days before randomization.
- Currently symptomatic (fever or chills, cough, myalgia, sore throat, shortness of breath, or new onset of anosmia or ageusia) and at COVID-19 isolation and treatment centre.

#### **7.2. Exclusion criteria**

- Inability to take orally administered medication or food.
- Known hypersensitivity to study medication.
- Pregnant or lactating (unless practicing exclusive replacement feeding for the entire study duration).
- Participation in any other interventional trial for COVID-19 (observational study co-enrollment allowed).
- Concurrent treatment with other agents with actual or possible direct-acting antiviral activity against SARS-CoV-2 less than 24 hours prior to study drug dosing.
- Concurrent use of agents with known or uncertain interaction with study drugs, including ritonavir.
- Requiring mechanical ventilation at screening.

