## 2.2. Atazanavir/ritonavir

The HIV protease inhibitor, atazanavir (boosted with ritonavir), has been shown to inhibit the major protease enzyme required for viral polyprotein processing during coronavirus replication. It also blocks pro-inflammatory cytokine production. Similar to nitazoxanide, atazanavir has been shown to achieve effective concentration pulmonary tissues at approved dose of 300 mg in combination with 100 mg of ritonavir, with even more favourable ratios when compared to *in vitro* activities generated in human cell models. Hence, it is a good candidate for drug repurposing in COVID-19. Additionally, nitazoxanide is inactivated by glucuronidation and atazanavir is a well-known inhibitor. Hence, when used in combination with nitazoxanide, atazanavir is expected to enhance nitazoxanide exposure.

Therefore, based on these considerations, the combination of nitazoxanide (taken orally at 1000 mg twice daily) and atazanavir/ritonavir (taken orally at 300/100 mg once daily) is selected as the intervention for this trial.

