## 13. Assessments of Nitazoxanide Pharmacokinetics

Following oral administration of 500 mg of nitazoxanide every 12 hours for 7 consecutive days in adults, the mean (SD)  $C_{max}$  of tizoxanide was 10.6 (2.1)  $\mu\text{g/mL}$  and no significant accumulation of nitazoxanide metabolites tizoxanide or tizoxanide glucuronide was detected. In a study that investigated nitazoxanide efficacy for pulmonary tuberculosis, a 1000 mg twice daily dose for 14 days was employed and no grade 4 or 5 adverse event was observed. The  $C_{max}$  of tizoxanide on days 5 and 14 were 11.3 (4.6)  $\mu\text{g/mL}$  and 9.0 (4.1)  $\mu\text{g/mL}$ , respectively. Therefore, to characterise the exposure-response relationship of tizoxanide when 1000 mg nitazoxanide is taken two times daily in combination with 300/100 mg atazanavir/ritonavir, pharmacokinetic (PK) sampling will be performed in trial participants on days 5 and 14 (intensive) and on days 3, 7, 10, 21, and 28 (sparse) based on the following schedule:

| Specimen               | Intensive pharmacokinetic (PK) sampling (n = 12)                                                | Sparse PK sampling (n = 49)                                                                                                                                                                    |
|------------------------|-------------------------------------------------------------------------------------------------------------|------------------------------------------------------------------------------------------------------------------------------------------------------------------------------------------------|
| Dried Blood Spot (DBS) | 0.5, 1, 2, 4, 6, 8 and 12 hours after dose on day 5
0.5, 1, 2, 4, 6, 8 and 12 hours after dose on day 14 | 12 hours after dose on day 2
12 hours after dose on day 4
12 hours after dose on day 6
12 hours after dose on day 7
12 hours after dose on day 14
12 hours after dose on day 28 |
| Saliva                 | 0.5, 1, 2, 4, 6, 8 and 12 hours after dose on day 5
0.5, 1, 2, 4, 6, 8 and 12 hours after dose on day 14 | 12 hours after dose on day 2
12 hours after dose on day 7
12 hours after dose on day 14                                                                                                  |

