## **17. Treatment Discontinuation and Withdrawal From Trial**

### **17.1. Discontinuation**

Study treatment may be discontinued for any of the following reasons:

- Request to terminate study treatment by participant

- Need to start concomitant medications known to interact with study intervention
- Development of any contraindication to study drug
- An adverse event that necessitates discontinuation of study drug
- Other reasons believed by the clinical investigators or primary care providers to place the participant at risk.

Where participants stop study intervention, they may continue in the trial off study drug with continued evaluations. The reason for study drug discontinuation will be documented.

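### No entry criterion covers known liver or kidney impairment or uses the Day 0 AST/ALT result, although Section 2.1 says nitazoxanide is unstudied in such patients

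*Protocol*

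**What the plan says.** Protocol Section 2.1, item 3, sets out nitazoxanide's safety record and closes with two limits. One is that "nitazoxanide safety during human pregnancy or lactation has not been evaluated". The other, in the next sentence, is that "it has not been studied in patients with renal or hepatic impairment".

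Section 2.2 explains that nitazoxanide is inactivated by glucuronidation and that atazanavir inhibits this route, so that "when used in combination with nitazoxanide, atazanavir is expected to enhance nitazoxanide exposure". It gives no size for the increase. Section 13 plans pharmacokinetic sampling within this trial "to characterise the exposure-response relationship of tizoxanide when 1000 mg nitazoxanide is taken two times daily in combination with" atazanavir/ritonavir.

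Section 7 states that "Eligibility will be ascertained using the following inclusion and exclusion criteria", and Sections 7.1 and 7.2 give the lists. Among the exclusions is "Pregnant or lactating (unless practicing exclusive replacement feeding for the entire study duration").

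Table 1 schedules a safety blood on Days 0, 7 and 14, and its footnote 1 says that the biochemistry includes AST and ALT. Dispensing of the trial drugs starts on Day 1. After entry, Section 17.1 allows treatment to be stopped for, among other reasons, "Development of any contraindication to study drug" and "Other reasons believed by the clinical investigators or primary care providers to place the participant at risk".

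**The concern.** The protocol identifies a population in which the main drug has no safety record, but its eligibility rules do not refer to that population. They do act on comparable uncertainty elsewhere. Pregnancy is excluded although Section 2.1 reports no teratogenicity in animals, and drugs whose interaction with the study drugs is merely uncertain are excluded in Section 7.2. For impaired patients the protocol neither excludes them nor says that it has chosen to include them.

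What is at stake is the safety of individual patients. Someone with known significant liver or kidney disease could receive 1000 mg nitazoxanide twice daily together with a drug expected to raise its exposure, and no entry rule would make anyone weigh organ function first. Liver results that could inform that decision are drawn on Day 0, but no criterion refers to them.

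**Working it through.** The protocol gives no figure to reproduce here. The check is a count of the criteria and a comparison of sections.

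**1. The entry criteria, in summary**

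| Section | Criterion | Concerns liver or kidney function, or uses AST/ALT? |
|---|---|---|
| 7.1 | Consent | No |
| 7.1 | Age 18 to 75 | No |
| 7.1 | PCR confirmation no more than 2 days before randomisation | No |
| 7.1 | Symptomatic, at a treatment centre | No |
| 7.2 | Unable to take oral drugs or food | No |
| 7.2 | Hypersensitivity | No |
| 7.2 | Pregnancy or lactation | No |
| 7.2 | Another interventional COVID-19 trial | No |
| 7.2 | Other antivirals in the preceding 24 hours | No |
| 7.2 | Interacting drugs | No |
| 7.2 | Mechanical ventilation at screening | No |

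Total: 4 + 7 = 11. Criteria on hepatic or renal function: 0 of 11. Criteria using the Day 0 AST/ALT: 0 of 11.

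**2. Section 2.1 against Section 7.2**

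| Limit named in Section 2.1 | Matching entry criterion |
|---|---|
| Pregnancy or lactation | Yes, Section 7.2 |
| Renal or hepatic impairment | None |

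One of the two limits is acted on at entry.

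**3. Dose and exposure**

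The trial dose is 2 × 1000 = 2000 mg/day. The usual dose cited in Section 2.1 is 2 × 500 = 1000 mg/day, so the trial doubles it before any effect of atazanavir. On the other side, Section 2.1 cites 1000 mg twice daily for 14 days as safe, up to 3000 mg/day for a median of 62 days without safety issues, and single doses up to 4000 mg in healthy volunteers. The same section says impaired patients have not been studied, so this reassurance does not extend to them.

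**4. Timing**

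Of the three safety bloods (Days 0, 7 and 14), only Day 0 precedes the first dose on Day 1. The next comes after Days 1 to 6, which is 6 × 2 = 12 scheduled nitazoxanide doses. Day 0 is therefore the only scheduled laboratory check that could keep an impaired patient from being dosed.

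**5. Whether another section closes the gap at entry**

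- Section 3.1 stratifies by relevant comorbidities. That governs allocation and excludes no one.
- Section 3.2 points to prescribing information in Appendix 4. No entry criterion invokes it.
- Section 17.1 concerns stopping treatment, not entry.
- Day 0 in Table 1 includes medical history and physical examination, so known disease would probably be noticed. No rule then acts on it.

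None of these is an entry rule.

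**The case against.** The strongest reply is that unstudied does not mean contraindicated. Section 2.1 states no hazard, dose limit or contraindication in impairment, and the protocol nowhere undertakes to exclude every unstudied group, so there is no formal contradiction. That stands, and it limits the point to a gap at entry.

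Safeguards after entry are also substantial: daily adverse event assessment, bloods on Days 7 and 14, weekly review of laboratory results by the Safety Review Committee, review of any grade 3 or higher event in the intervention group (including by the IDSMC), and a safety review once 15 intervention participants have completed 14 days. These stand too, but they act on patients already enrolled.

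Three stronger readings are tempting and are not supported:

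- A reader might infer that kidney function is not measured, since footnote 1 names only AST and ALT while Section 5 lists acute kidney injury as a safety outcome. The footnote's biochemistry list is open-ended and may include creatinine, so absence is not shown.
- A reader might infer that Section 17.1 helps only with problems that arise on treatment. The clause on perceived risk, "Other reasons believed by the clinical investigators or primary care providers to place the participant at risk", does not require the risk to be new. A clinician who saw an abnormal Day 0 result could stop treatment under it. This is discretion, however, and not an entry rule.
- A reader might infer that impairment is a labelled contraindication to either drug. Appendix 4 shows only headings and links, so this cannot be judged from the document.

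**Conclusion.** The point holds as a modest patient-safety gap confined to entry. The protocol calls nitazoxanide unstudied in renal or hepatic impairment and expects the combination to raise its exposure, yet 0 of 11 criteria address such impairment or use the Day 0 liver results. Patients with known significant disease can be randomised and, in the intervention arm, dosed.

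Its size cannot be put as a number of patients, because the protocol gives no prevalence of impairment among those it will recruit. Endpoints, power and analysis are unaffected, and no harm is demonstrated. The conclusion assumes that the two lists are the whole basis for eligibility, as Section 7 indicates. A deliberate choice to include impaired patients would be defensible if it were stated and justified, but the protocol does neither. The change should be made because it is cheap and protects patients.

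**What to change.** Add to Section 7.2 an exclusion for clinically significant hepatic or renal impairment, whether already known or evident on the Day 0 safety blood, with cut-offs set by the clinical team. COVID-19 may itself disturb these tests, which is a reason to limit the exclusion to clinically significant impairment.

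Require the Day 0 result to be reviewed before the first dose on Day 1, and before randomisation where laboratory turnaround allows. If a disqualifying result arrives after randomisation, withhold the drug but keep the patient in follow-up and in the randomised comparison. Section 3.4 already takes this approach for participants who stop treatment. Confirm that creatinine is in the Day 0 panel.

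The cost is an amendment to Section 7.2 and an update to the eligibility form. The Day 0 blood is already scheduled, so no draw is added. The downsides are an unknown number of patients screened out and a possible short delay. The delay must fit two windows: recruitment within 2 days of admission (Section 3.1) and PCR confirmation within 2 days before randomisation (Section 7.1). The protocol gives no turnaround time, so sites should check this before the rule is fixed.
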